3.3 Main study visits

After the subject has entered the study, s/he will come to the Indiana Clinical Research Center for the initial Week 0 (Entry) visit within three weeks of the screening visit. The subject’s medical records will be re-examined for clinical variables of interest. Adherence to study drug will be assessed by pill count, three-day recall, and eventually by PTX level which will be measured in batch at the end of each trial. To assess the success of the blinding mechanism/allocation, both the subjects and study nurse will be asked if they thought the subject was randomized to either PTX or placebo at study closeout.

Vital signs and anthropometrics will be measured per AIDS Adult Clinical Trials Group recommendations (<http://aactg.s-3.com/members/download/other/metabolic/>). The subject will provide fasting, morning blood samples for markers of cardiovascular risk, inflammation, endothelial activation, immune activation, and metabolism. All specimens not required for real-time safety monitoring will be frozen and batch-tested at the end of these studies to reduce interassay variability. The lone exception will be the flow cytometry measurements for activated CD8 cells, which will necessarily be performed on fresh whole blood samples.

The subject will then undergo brachial artery reactivity testing as outlined by the International Brachial Artery Reactivity Task Force [130]. The procedure for measuring brachial reactivity will require one hour of the subject’s time. There will be no documentation on the ultrasound scans regarding the HIV status (HIV-positive for the trial participants vs. HIV-negative for the external control subjects) or the randomization assignment of the participants in the two trials. This will ensure that [name], who will assess all the ultrasound results, will be blinded to these two key variables. All members of the study team will be blinded to the drug assignment for those subjects in the clinical trials. Female participants of reproductive potential will have their main study visits during the same phase of their menstrual cycle to minimize confounding by hormonal changes that may affect FMD results [131, 132]).

As a safety measure, a peripheral IV heplock will then be placed at the IU ICRC to reduce the number of venous punctures required for the serial blood draws required to estimate insulin resistance. The heplock will also facilitate the infusion of IV fluids if NTG-induced hypotension occurs during the brachial artery reactivity testing. By performing just one venous puncture for placement of the IV heplock, the risks of bleeding, bruising, pain, and infection to the subject will be minimized; this will also reduce the risk of accidental occupational exposure of potentially infectious material to the study team. The heplock will then be removed after assurance of subject hemodynamic stability once brachial reactivity testing is completed.

Safety and adverse events will be assessed at each study visit. Study participants will be encourage to notify the study team in between these visits if symptoms occur that may be related to study drug. In the event of an adverse event possibly related to study drug, a full assessment (examination, laboratories) will be performed immediately. Study discontinuation will occur if a Grade 3 or 4 event (per Division of AIDS Toxicity Grading System <http://roc.s-3.com/members/download/adulttox.pdf>), serious adverse event, or hospitalization likely due to study drug occurs. For less severe events thought to be related to study drug, then PTX or placebo dosing will be reduced by one pill (e.g. 400mg of active agent) and symptoms, signs, and laboratories will be reassessed after one week. If the adverse event continues at the same severity or improves only modestly, then dosing will be reduced by one more pill and again the participant will be reassessed after one week. If the adverse event persists at this time, then the subject will be discontinued from the study. However, if symptoms resolve after dose reduction, then the subject will continue on study using the new dosage level. The subject, of course, will have the option of withdrawing from the study at any time. All subjects who stop study drug prematurely due to an adverse event will be followed weekly until resolution. Please see Human Subjects Protection for further details on safety monitoring.

3.4 Brachial artery reactivity indices

The brachial artery diameter will be measured according to established guidelines [130] at baseline and in response to two stimuli: (1) endothelium-dependent vasodilation due to increased blood flow, or Flow-Mediated Dilation (FMD), and (2) endothelium-independent vasodilation due to sublingual nitroglycerin, or Nitroglycerin-Mediated Dilation (NTGMD). The same operator, blinded to case/control status of the subjects, will perform all studies.

Brachial reactivity measurements are subject to considerable day-to-day variability. Variables that will transiently affect vasomotor function include environmental conditions, tobacco and alcohol use, diet, and medications [133]. Therefore, it is desirable to control these factors in order to obtain results that more accurately reflect the underlying condition being studied. Therefore, the room temperature will be controlled at 68-71F. The subject will rest supine for 10 minutes prior to imaging. Subjects will be told to not use tobacco-containing products or eat or drink anything other than water for 12 hours prior to the study. Female subjects will first have urine pregnancy testing performed prior to the ultrasound tests; if the subject is found to be pregnant, the subject’s participation will end. If any of the systolic blood pressures measured on either of the main study visits is <90mm Hg, then the visit must be rescheduled.

A 10 mHZ linear array vascular probe for B-mode imaging will be used to visualize the brachial artery. Data will be stored on a compact disc (for primary data analysis); these ultrasound data will also be backed-up on magneto-optical disks and the IU server with password protection. ECG leads will be placed on the subject’s chest and automatic blood pressure cuff to left upper arm, set at q.15 minutes. A small forearm cuff is placed on the widest part of the subject’s proximal right forearm (approximately 1-2 cm distal to the antecubital fossa). The brachial artery will then be located with the image optimized for best resolution of all three layers of the anterior and posterior walls (with special emphasis on identifying the media-adventitia interface). Three consecutive cardiac cycles of B-mode images of the brachial artery to the disks will be acquired and stored.

After this baseline evaluation, the measurement of endothelium-dependent vasodilation, or FMD, due to increased blood flow will begin. The forearm pressure cuff will be inflated to 250 mmHg for 5 minutes. At that time, imaging will be switched to B-mode. At 60 and 90 seconds after cuff deflation, three consecutive cardiac cycles of B-mode images of the brachial artery to the disc will be acquired and stored. The greater of the two diameters measured at these time points will be used for FMD analysis.

After 15 minutes from time of cuff deflation, the measurement of endothelium-independent vasodilation, or NTGMD, will begin. As before, three consecutive cardiac cycles of B-mode images of the brachial artery stored to the disc. Blood pressure measurement will then be repeated as a new baseline. Nitroglycerin (400 mcg SL) will then be administered. Three minutes later, three consecutive cardiac cycles of B-mode of the brachial artery stored to the disc and backed-up to a magneto-optical disk and the IU server with password protection.

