1. CLINICAL AND LABORATORY EVALUATIONS

6.1 Schedule of Events

| **Evaluations** | **Screening** | **Study Visits** | | |
| --- | --- | --- | --- | --- |
| **-21 to -7 Day(s)** | **Week 0/**  **Entry** | **Week 4**  **Days 28-42** | **Week 8/Closeout**  **Days 56-70** |
| **Documentation of HIV Status** | X |  |  |  |
| **Medical History** | X |  |  |  |
| **Medication History** | X |  |  |  |
| **Concomitant Medications** |  | X | X | X |
| **Pentoxifylline/Placebo Dosing Modifications** |  | Anytime after entry based on adverse side effects | | |
| **Family History** |  | X |  |  |
| **Smoking History** |  | X |  |  |
| **Brief Physical Examination** | X | X | X | X |
| **Signs & Symptoms** |  | X | X | X |
| **Diagnoses** |  | X | X | X |
| **Adherence Questionnaire** |  |  | X | X |
| **Assessment of effective blinding** |  |  |  | X |
| **Height** |  | X |  |  |
| **Weight** | X | X | X | X |
| **Vital Signs** | X | X | X | X |
| **Waist/Hip Circumferences** |  | X | X | X |
| **Serum Creatinine** | X | X | X | X |
| **Calculated Creatinine Clearance** | X | X | X | X |
| **Liver Function Tests** | X | X | X | X |
| **Urine Pregnancy Test** | X | Whenever pregnancy suspected | | |
| **Urine Analysis** |  | X | X | X |
| **Hematology** | X | X | X | X |
| **CD4/CD8 cell counts and percentages** | X | X | X | X |
| **HIV-1 RNA Level (viral load)** |  | X | X | X |
| **Hepatitis B/C Serologies** |  | X |  |  |
| **PTX Levels** |  | X | X | X |
| **Whole blood for Advanced Flow Cytometry for Immune Activation (CD8+/CD38+/HLA-DR+ cells)** |  | X |  | X |
| **Frozen Serum/Plasma/Urine for Glucose, Insulin, Lipids, Albuminuria, Inflammatory and Endothelial Activation Markers** | X | X | X | X |
| **Frozen Plasma, Serum, & Urine for Future Studies** |  | X | X | X |
| **Brachial Artery Reactivity Testing** |  | X | X | X |

- 1. Definitions for Schedule of Events – Timing of Evaluations

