6.3.8.13 Brachial artery ultrasound measurements

All brachial artery ultrasound measurements must be recorded on CRFs. If any of the systolic blood pressures measured on either of the main study visits prior to brachial artery ultrasound measurements is <90mm Hg, then the visit must be rescheduled.

Perform the assessment in the morning to avoid adrenergic stimulation after an overnight fast (approximately 8 hours).

Subjects may not use tobacco-containing products or eat or drink anything other than water for 8 hours prior to the assessment and until it is completed. See section 3.4 for the ultrasound procedure.

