1. CRITERIA FOR STUDY DISCONTINUATION

- Request by the subject to withdraw
- Request of the primary care provider if s/he believes the study is no longer in the best interest of the subject
- If the subject is found to be pregnant or begins breastfeeding during the course of this study
- If the subject has develops fever, need for systemic therapy for acute or serious illness, or hypotension after screening that precludes completion of the main study visits within the allowed timeframes
- If the patient develops a need for antiretroviral therapy, as determined by the Principal Investigator or by the subject’s primary HIV caregiver
- Requirement for prohibited concomitant medication(s)
- Study drug-related toxicity (see section 7.0 Adverse Event Management)
- Clinical reasons believed life threatening by the physician
- Subject, as judged by the investigators, to be at risk of failing to comply with the provisions of the study protocol as to cause harm to self or interfere with the validity of the study results
- At the discretion of the funding agency

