10.3.2 Protection Against Risk

10.3.2.1 Confidentiality. To minimize the risk to subject confidentiality, patient identifiers will be removed once his or her data is abstracted and recorded, and only the random study identification number (generated when consent is provided) will be used. All hardcopy study data will be kept in a secured and locked file cabinet. All electronic data will be kept in a password-protected computer database. The only link between patient identifiers and the randomized study identification number will be kept in separate files. Identifiers will never be used in the analysis or presentation of study results.

10.3.2.2 Blood draws. The risks of blood drawing will be minimized by having only experienced medical personnel perform this procedure. The amount of blood that will be drawn falls well within safety standards for blood donation.

10.3.2.3 Pentoxifylline. Our pilot data and safety results from the literature suggest that PTX is very well-tolerated, so we do not expect any serious adverse events from use of this agent. However, to minimize potential risks with this drug, the eligibility criteria will reduce the potential adverse events associated with this drug by excluding those at higher risk. Adverse events will be monitored for closely. Safety laboratories (complete blood cell counts including platelet counts, chemistries, renal and liver function tests) will be obtained at each main study visit or upon development of symptoms. Grade III or IV abnormalities (defined using the Division of AIDS Table for Grading Adult Adverse Experiences) will prompt immediate discontinuation of the drug. Pregnant and breastfeeding women will be excluded. Women of reproductive age will be asked to use two forms of contraception during the clinical trials.

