10.7 Inclusion of Women and Minorities

There are no exclusion criteria based on gender, racial category, or ethnicity in the proposed studies. Please see the attached Targeted/Planned Enrollment Table. Based on our previous cumulative experience and the general HIV-infected population cared for at the study sites at Indiana University, it is anticipated that approximately 25% of the study subjects will be women. Pregnant women will be excluded due to the confounding effects of pregnancy on cardiovascular physiology and because pentoxifylline is a Pregnancy Category C agent; we will ask all women of reproductive potential to use two forms of contraception during study participation. Breastfeeding women will also be excluded due to the presence of PTX in the breastmilk of women using pentoxifylline.

It is anticipated that approximately 40% and 8% of the study subjects will be black and Hispanic, respectively. American Indians, Alaskan Natives, Asians, Native Hawaiians or Other Pacific Islanders are not expected to be represented in the proposed study population due to extremely low representation of these groups within the Indiana University Medical Center outpatient clinics and in Indianapolis in general.

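### Section 3.4 requires a urine pregnancy test before the ultrasound scans, but the Schedule of Events has no routine test after screening, so a site working from the Schedule would dose on a test 7 to 21 days old

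*Combined protocol and SAP*

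**What the plan says.** Section 3.4 (Brachial artery reactivity indices) reads: "Female subjects will first have urine pregnancy testing performed prior to the ultrasound tests; if the subject is found to be pregnant", and the consequence is that she leaves the study. The sentence stands among same-day preparations: room temperature, supine rest, fasting, and rescheduling if systolic pressure is below 90 mmHg.

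The Schedule of Events (Section 6.1) places brachial artery testing at Week 0, Week 4 and Week 8. Its urine pregnancy row has an X under screening (Day -21 to Day -7) and, across the three study visits, only "Whenever pregnancy suspected". Section 3.2 separately requires a test at screening for women of reproductive potential.

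Other provisions bear on the point:

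- Section 6.3.8.13 repeats the systolic pressure rule but not the pregnancy test. It does direct staff onward: "See section 3.4 for the ultrasound procedure".
- Section 10.3.2.3: "Safety laboratories (complete blood cell counts including platelet counts, chemistries, renal and liver function tests) will be obtained at each main study visit". That list does not include a pregnancy test. The same section adds: "Women of reproductive age will be asked to use two forms of contraception during the clinical trials".
- Section 10.7 repeats the contraception request ("we will ask all women of reproductive potential to use two forms of contraception during study participation"). It gives two reasons for excluding pregnancy: the drug is Category C, and pregnancy confounds cardiovascular physiology.
- Pregnancy is an exclusion in Section 4.2. Section 8 lists as a reason to discontinue: "If the subject is found to be pregnant or begins breastfeeding during the course of this study".

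**The concern.** One section makes the test a precondition of scanning. The other makes it depend on suspicion from entry onward. Clinic staff commonly work from the visit schedule, and a coordinator who did so here would skip a check that the procedure text requires.

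Two things are at stake. The first is safety: an unsuspected pregnancy could be exposed to pentoxifylline and nitroglycerin. Section 2.4.5 reports no fetal malformation in rats or rabbits but increased resorption at the top rat dose, so the hazard should not be exaggerated, yet the protocol itself chose to exclude pregnancy. The second is measurement: a pregnant subject's flow-mediated dilation (FMD) values would enter the primary endpoint, although Section 10.7 names pregnancy as a confounder of the physiology that FMD measures.

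**Working it through.** **Where the two rules conflict**

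| Visit | Scan? | Section 3.4 | Schedule row |
| --- | --- | --- | --- |
| Screening (Day -21 to -7) | No | not addressed (Section 3.2 requires a test) | X |
| Week 0 | Yes | test before scan | only if suspected |
| Week 4 (Day 28-42) | Yes | test before scan, if every scan is meant | only if suspected |
| Week 8 (Day 56-70) | Yes | test before scan, if every scan is meant | only if suspected |

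Section 3.4 does not say that the test precedes each scan. Read narrowly (before the first scan), the sections conflict at Week 0. Read broadly (before every scan), they conflict at all three visits.

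**Age of the last routine test if only the Schedule is followed**

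Age = visit day minus screening day, taking the first dose to be on the day of entry (assumption).

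- Entry: 0 - (-7) = 7 days to 0 - (-21) = 21 days. The 7-day minimum comes only from the Schedule header; Sections 3.3 and 6.2.1 give just the 21-day maximum, which would make the range 0 to 21 days.
- Week 4: 28 + 7 = 35 days to 42 + 21 = 63 days.
- Week 8: 56 + 7 = 63 days at the shortest. The stated maximum of 11 weeks (Sections 3.5 and 10.3.2.5) gives 11 × 7 = 77 days. The outer windows combined would give 70 + 21 = 91 days, which exceeds that maximum.

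**Under Section 3.4 read as every scan**

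The test is same-day at each visit. The longest gap between tests on study drug is 42 - 0 = 42 days (Day 0 to a late Week 4 visit) or 70 - 28 = 42 days (an on-time Week 4 visit to a late Week 8 visit).

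**How many subjects this concerns**

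Section 10.7 says "it is anticipated that approximately 25% of the study subjects will be women". Expected number: 0.25 × 26 = 6.5. If 25% is the true share and enrolment is independent (assumption), the number of women is Binomial(26, 0.25), and P(3 ≤ X ≤ 11) = 0.959. At an even split between arms (assumption), 6.5 / 2 = 3.25 women would be on pentoxifylline. These figures count women. The documents give neither the share of reproductive potential nor a pregnancy rate, so they cannot be turned into an expected number of pregnancies.

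**The case against.** The strongest reply is that the two sections can be reconciled. The screening test in Section 3.2 precedes every ultrasound, so it literally satisfies a requirement to test beforehand, and Section 3.4 says neither each scan nor the same day. This reading is strained. The sentence in Section 3.4 sits among scan-day steps, orders the test first, and attaches its own consequence (participation ends). If the screening test met it, the sentence would add nothing to Section 3.2.

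A second reply is that the Schedule is merely incomplete: it does not forbid a test at the visits, and Section 6.3.8.13 sends staff to Section 3.4. One operator does all the scans at one centre, and a site that reads both sections will test before the scan. This stands in part: the gap opens only if Section 3.4 is overlooked. Section 6.3.8.11 also lists pregnancy-test values for the case report forms, but it lists the entry-only hepatitis serologies too, so it does not establish a test at every visit.

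A third reply is that other safeguards make harm unlikely: requested contraception, testing on suspicion, the exclusion and discontinuation criteria, and visits matched to menstrual phase with the last period recorded (Sections 3.3 and 6.3.2). These are real and lower the risk. None is a routine test, and the discontinuation criterion acts only once a pregnancy has been found.

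Some supporting signs are also weak. The safety laboratories in Section 10.3.2.3 are mainly blood tests for drug toxicity, and vital signs would be scheduled at every visit whatever Section 3.4 said. The finding does not depend on either.

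**Conclusion.** The concern holds. Two operative sections give different instructions for the same participant-safety check, and the protocol does not say which takes precedence. A site following the Schedule alone would give the first dose on a pregnancy test 7 to 21 days old, where Section 3.4 calls for a test before the scan; by the last visit that test could be 77 days old within the stated study maximum. This rests on the Schedule's screening window, on first dosing at entry, and on staff not acting on Section 3.4.

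The conflict affects safety conduct and the cleanliness of individual FMD values. It does not touch type I error, power or sample size. It should be fixed, at the low end of that category.

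**What to change.** 1. **Section 6.1, urine pregnancy row:** mark X at Screening, Week 0, Week 4 and Week 8 for women of reproductive potential, and keep testing on suspicion as an addition.
2. **Section 3.4:** replace the sentence with wording such as: *At Weeks 0, 4 and 8, a negative urine pregnancy test is required before the scan and nitroglycerin and, at Week 0, before the first dose of study drug.*
3. **Optional:** repeat the rule in Section 6.3.8.13 beside the systolic pressure rule, and use one description of the women concerned throughout (the text now varies between female subjects, women of reproductive age and women of reproductive potential).

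Section 3.4 leaves open whether every scan is meant. Testing at all three visits settles this in the safer direction.

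**Cost:** three Schedule cells and one sentence. Three dipsticks per woman come to 3 × 6 = 18 to 3 × 7 = 21 at the expected enrolment, or 3 × 3 = 9 to 3 × 11 = 33 across 3 to 11 women. Urine is already collected at these visits for urinalysis, and Section 6.3.8.11 already requires the results on case report forms. Visits, sample size and analysis do not change.

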3.5 Study Duration and Subject Retention

The maximum study period for each subject will be 11 weeks (screening phase of 3 weeks and main visit phase of 8 weeks). In order to promote retention in the study, the subject participants will be financially compensated for each screening and main visit.

4.0 SELECTION AND ENROLLMENT CRITERIA

4.1 Inclusion Criteria

4.1.1 HIV-1 infection, documented by (1) any licensed rapid HIV test or HIV enzyme or chemiluminescence immunoassay (E/CIA) test kit at any time prior to study entry and confirmed by a licensed Western blot or a second antibody test by a method other than the initial rapid HIV and/or E/CIA, or (2) by two detectable HIV-1 antigens, or (3) two detectable plasma HIV-1 RNA viral loads.

- - 1. Age equal to or greater than 18 years.
    2. CD4 cell count > 350/µL at screening.
    3. No receipt of any antiretroviral therapies within the six months prior to screening.
    4. No anticipated need for any antiretroviral therapies during the course of this study, as determined by the principal investigator or by the subject’s HIV caregiver.

Note: There is no HIV-1 RNA level eligibility criterion.

